#### Costs

To assess a participant’s medical consumption and productivity cost items from the iMedical Consumption Questionnaire (iMCQ) and iProductivity Cost Questionnaire (iPCQ) will be used after 3 and 6 months. These questionnaires were targeted to our study population of people with T2DM. By using both the iMCQ and iPCQ, costs will be measured from a societal perspective, considering health care use, homecare, work presenteeism and work absenteeism [39, 40]. A participant’s prescribed medication is obtained from the pharmacy information system.

### Participant time line {13}

When participants are enrolled in the study (i.e. after the informed consent procedure), they will fill in the first questionnaire (i.e. Adapted QBS, Demographics, MARS-5, BMQ Specific, DTSQs and EQ-5D-5L). After the first questionnaire, participants will be randomised to either the intervention or control group. Following randomisation, telephone pill counts will be conducted and blood pressure and HbA1c values will be obtained from registry data. One month after the personalised intervention programme was initiated, a satisfaction phone call will be conducted with participants that are randomised to the intervention group. Three and 6 months after study start, participants respectively will fill in the second (i.e. MARS-5, BMQ Specific, DTSQs, EQ-5D-5L and iMTA costs) and third questionnaires (i.e. MARS-5, BMQ Specific, DTSQs, DTSQc, EQ-5D-5L and iMTA costs). Table 2 provides an overview of all the assessments according to the SPIRIT, and Fig. 1 presents a schematic overview of the study design of the INTENSE study.

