### Outcomes {12}

#### Primary outcome measure

The primary outcome measure of the study is medication adherence assessed with a telephone pill count that is carried out based on a previously validated approach ([name], [name], [name], [name], [name], [name]: Validation of an announced telephone pill count compared to a home-visit pill count in people with type 2 diabetes or cardiovascular disease, Submitted). A member of the research team will conduct the telephone pill count with the use of a standardised protocol. The participant will be asked to gather all of their medication and count the number of remaining pills from their oral antidiabetic and/or antihypertensive medication. Calculation of the pill count will be performed by using the following equation: (number of dosage units dispensed − number of dosage units remaining) / (prescribed number of dosage units per day × number of days between two telephone pill count 1 and count 2) [32].

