#### Secondary outcome measures

The secondary outcome measures of the study are systolic blood pressure, HbA1c level, self-reported medication adherence, attitude and beliefs toward medication, satisfaction with diabetes treatment, health status and medical consumption and productivity cost. An overview of all the assessments is presented in the Standard Protocol Items Recommendations for Interventional Trials (SPIRIT) diagram in Table 2.

**Table 2 Tab2:** SPIRIT diagram (*t*_0_= baseline; *t*_1_=1 month after baseline; *t*_2_=3 months after baseline; *t*_3_=6 months after baseline) [33]. ^*^Satisfaction phone call will only be performed in participants that receive the intervention condition

	Study period						
	Enrolment	Pre-randomisation	Randomisation	Post-randomisation			
**TIME POINT**				t_0_	t_1_	t_2_	t_3_

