##### Systolic blood pressure and HbA1c level

To assess a participant’s systolic blood pressure and HbA1c level at baseline, general practice registry data will be consulted with a time window of 3 months before to 1 month after the time point. At the end of the follow-up, general practice registry data will also be consulted, but with a time window of 2 months before to 2 months after the time point. Data will be collected through a telephone call conducted by a member of the research team.

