### Implementation {16c}

As soon as a member of the research team has indicated in the data management platform Castor EDC that the participant is suitable for the study and that the participant has given informed consent, allocation will be indicated by Castor EDC [29].

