## Assignment of interventions: blinding

### Who will be blinded {17a}

Blinding of the research team, pharmacy team, participants and GPs to treatment allocation is not possible due to the nature of the study.

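### In an open trial, the first pill count falls after allocation and baseline SBP/HbA1c readings may do so too, so the arm can influence them

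*Protocol article*

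**What the plan says.** The protocol article fixes the order of events. On the questionnaires, Participant time line {13} says: "After the first questionnaire, participants will be randomised to either the intervention or control group". The next sentence puts the other baseline measurements later: "Following randomisation, telephone pill counts will be conducted and blood pressure and HbA1c values will be obtained from registry data".

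Table 2 gives the same order. It has a pre-randomisation column, which holds the Adapted QBS, demographics, MARS-5, BMQ Specific, DTSQs and EQ-5D-5L. Baseline (t0) is the first column under the heading "Post-randomisation", and the pill count, blood pressure and HbA1c are marked there.

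For baseline SBP and HbA1c, the section Systolic blood pressure and HbA1c level says that "general practice registry data will be consulted with a time window of 3 months before to 1 month after the time point".

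On blinding, section {17a} says: "Blinding of the research team, pharmacy team, participants and GPs to treatment allocation is not possible due to the nature of the study". On the primary outcome, the section Primary outcome measure says: "A member of the research team will conduct the telephone pill count with the use of a standardised protocol". The participant counts the remaining pills, and the adherence formula runs over the days between count 1 and count 2.

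**The concern.** A baseline value is protected by randomisation only if it is fixed before anyone can act on the allocation. Here the self-report instruments have that protection. The first pill count does not, and SBP and HbA1c have it only in part.

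**SBP and HbA1c.** A reading up to 1 month after t0 still counts as baseline. Table 2 places t1, the satisfaction call in the intervention arm, at that same 1-month point. By then a medication review or GP referral may have taken place in the intervention arm only. Taking change from such a value, or adjusting for it, removes part of the effect that the trial is meant to estimate. The two outcomes are secondary, but the sample size section names target differences for both.

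**Pill count.** Count 1 is the starting point of the primary-outcome interval. If the participant or the caller knows the arm, or if the pharmacist appointment has already changed how medication is kept or supplied, the reported opening stock can differ between arms for reasons other than pills taken. The document does not say whether count 1 comes before or after the appointment.

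**Working it through.** No sample size, power or alpha in the plan depends on this point, so there is no stated figure to reproduce. The check sets out the sequence and then sizes the consequence under stated assumptions.

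**1. Sequence.** Text and Table 2 both give: consent, first questionnaire, randomisation, then t0 with count 1 and the SBP/HbA1c retrieval. The 1 month in the registry window is counted from t0. The interval from randomisation to t0 is not stated, so a baseline reading could lie more than 1 month after allocation.

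**2. Inputs from the article.**
- Baseline window: 3 months before to 1 month after t0.
- Programme length: 6 months (Intervention description {11a}).
- Target differences Δ: 5 mmHg SBP and 0.5% HbA1c (Sample size {14}).

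**3. Assumptions, not in the article.**
- Reading dates are spread evenly over the window, and the programme starts at t0.
- The effect either builds linearly over 6 months or, as an extreme, is complete at once.
- The analysis uses change from baseline, or baseline as a covariate with slope b = 0.5.

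**4. Share of readings after t0.** s = 1/(3 + 1) = 0.25.

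**5. Fraction of the effect already present in those readings.** Linear: mean elapsed time is 0.5 month, so g = 0.5/6 = 0.083. Immediate: g = 1.

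**6. Results.** Baseline shift = s × g × Δ. Change-score estimate = Δ(1 − s·g). Covariate-adjusted estimate = Δ(1 − b·s·g).

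| Case | Outcome | Shift | Change score | Covariate, b = 0.5 |
|---|---|---|---|---|
| Linear | SBP | 0.25 × 0.083 × 5 = 0.10 mmHg | 4.90 of 5 | 4.95 |
| Linear | HbA1c | 0.25 × 0.083 × 0.5 = 0.01% | 0.49 of 0.5 | 0.495 |
| Immediate | SBP | 0.25 × 1 × 5 = 1.25 mmHg | 3.75 of 5 | 4.375 |
| Immediate | HbA1c | 0.25 × 1 × 0.5 = 0.125% | 0.375 of 0.5 | 0.438 |

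The change-score loss is s·g = 0.25 × 0.083 = 2.1% in the linear case and 25% in the immediate case.

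**7. Sensitivity to the even-spread assumption.** With s = 0.1 the losses are 0.1 × 0.083 = 0.8% (linear) and 10% (immediate). With s = 0.5 they are 4.2% and 50%. So 25% is the upper figure under an even spread, not a bound for every pattern of dates. With only readings dated on or before randomisation, s = 0 and the shift is 0 by design.

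**8. Primary outcome.** Adherence is units used divided by (prescribed units per day × days between counts). If the units used are reckoned from the stock in hand at count 1, an error of e units moves a participant's result by e/(units per day × days). For scale only, assume one unit a day and 6 × 30 = 180 days: each miscounted unit moves adherence by 1/180 = 0.56 percentage points. At two units a day it is 0.28. The article gives nothing from which to estimate e, or its difference between arms.

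**The case against.** **Retrieval is not measurement.** SBP and HbA1c are looked up after randomisation, but three of the four window months lie before t0, so under an even spread most values cannot have been affected. This stands. A reader might infer that all baseline SBP and HbA1c values are post-treatment; the text does not support that.

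**No baseline model is stated.** The article specifies multilevel regression, not change scores or a baseline covariate. This stands, and it makes the SBP/HbA1c bias conditional on how the values are used. Time is named as a level in the sample size section, so use of baseline values is plausible but not stated.

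**Count 1 is not a baseline adherence score.** Correct. The attenuation argument does not carry over to the primary outcome. What remains there is arm-related error in the opening stock. The standardised protocol reduces that risk, and count 2 is open to the same knowledge in any case, so moving count 1 removes only part of it.

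**Readings of the text that go too far.**
- A reader might infer that people who withdraw on learning their arm lose the primary outcome because count 1 comes late. They would lack count 2 as well, so an earlier count 1 would not make the outcome computable.
- A reader might see a contradiction in Implementation {16c}, where once suitability is entered and "the participant has given informed consent, allocation will be indicated by Castor EDC", the arm is known. That section does not say when the entries are made. They can follow the questionnaire, so it is compatible with the time line.
- The possible gap between baseline and follow-up readings runs from 6 − 2 − 1 = 3 to 6 + 2 + 3 = 11 months. That applies to both arms and does not itself show a treatment-affected baseline.

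The design figure is not available here, but text and Table 2 are explicit and agree.

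**Conclusion.** The point holds in limited form and should be fixed. The article itself places count 1 after allocation in an unblinded trial and accepts baseline SBP and HbA1c readings up to 1 month after t0. Nothing else in it corrects either rule.

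For SBP and HbA1c, if these values are used as baseline, the bias is toward no effect. It is about 2% of the target difference with evenly spread dates and a linear build-up, and about 25% with an immediate full effect. The linear figure shows that the bias may well be small. For the primary outcome the route is direct, but its size cannot be derived from the document. The sample size is unaffected, and the documents do not support a claim that the primary comparison is invalid.

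**What to change.** 1. Define baseline SBP and HbA1c as the latest registry value in the 3 months up to and including the randomisation date. Treat later values as missing baseline under the multiple imputation already planned.
2. Make count 1 after the first questionnaire and before Castor EDC releases the allocation.
3. Bring the section Systolic blood pressure and HbA1c level, Participant time line {13} and Table 2 into line with these rules.
4. For participants already enrolled, apply the same date rule to SBP and HbA1c, and report the timing of count 1 relative to allocation by arm.

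**Cost.** A few more baseline SBP and HbA1c values will be missing and need imputation. The workflow changes during recruitment, on a separate Castor platform in each country. Count 1 will have two timings across the trial, which is why its timing should be reported. A few days before the programme starts will also fall inside the adherence interval, slightly diluting the contrast in the intervention arm. These costs are modest, and no sample size changes.

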**Fig. 1 Fig1:**
[figure not shown]
Schematic overview of the study design of the INTENSE study

### Sample size {14}

The sample size calculation was based on multilevel analysis with the pharmacy, patient and time as different levels and we assumed a relative difference of 20% in medication adherence between the intervention and control group [41]. The relative difference was based on what the study team deemed to be clinically relevant. Both in the intervention and control groups, 98 participants are needed, considering a type I error rate of 5% and power of 0.80. In addition, taking the cluster design of the study into account, and assuming an intra-correlation coefficient of 0.10, a total of 110 participants are needed in both trial arms. To adjust for an expected loss to follow-up of 25%, we will need to include 145 participants in both the intervention and control group. In total, 300 participants will be included, namely 150 in the Netherlands and 150 in the UK. Additional power calculations for the secondary outcomes showed that this would also be sufficient to detect a difference of 0.5% in HbA1c and 5 mmHg in systolic blood pressure.

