**Methods:**

A parallel-group randomised controlled trial will be conducted in 40–50 community pharmacies in the Netherlands and the United Kingdom (UK). A total of 300 participants will be included and followed up for a period of 6 months. Participants will be people with T2DM identified as non-adherent to oral antidiabetic and/or antihypertensive medication, aged 35–75 years and mobile phone users. The intervention group will receive a personalised intervention programme that is based on one or more of the participants’ pre-defined non-adherence profile(s), namely (I) Knowledge and perceptions, (II) Practical problems, (III) Side effects and (IV) Negative mood and beliefs. The intervention comprises of one or more supporting modules, namely (I) Brief messaging, (II) Clinical medication review, (III) Medication schedule, (IV) Reminding messaging, (V) Medication dispensing systems, (VI) Smart messaging, (VII) Referral to general practitioner and (VIII) Unguided web-based Self Help Application for low mood. The control group will receive usual care including access to a publicly available informative diabetes website. The primary study outcome is medication adherence measured with a telephone pill count. Secondary outcomes are systolic blood pressure, HbA1c level, self-reported medication adherence, attitude and beliefs toward medication, satisfaction with diabetes treatment, health status and medical consumption and productivity cost. In addition, a process evaluation will be undertaken to establish the fidelity, reach and the extent to which intervention delivery is normalised in the daily practice of community pharmacy teams.

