### Recruitment {15}

#### Pharmacy and general practice recruitment

In the Netherlands, pharmacies will be recruited throughout the country. Pharmacies will be provided with an information sheet via email entailing details about the study. When pharmacies express interest in participation in the study, a member of the research team will contact them via telephone and provides them with additional information after which pharmacies can decide if they want to participate in the study. Participating pharmacies will receive a voucher of €25 for every participant they guide during the study. General practices that will be consulted for registry data on participants’ HbA1c and blood pressure levels will not actively be recruited since they are participants’ caregivers and will receive a voucher of €15 for every participant.

In the UK, remuneration of pharmacies and medical practices will be in accordance with nationally agreed UK tariffs for research. Calculations will include remuneration for medical practices to screen and invite eligible patients and provide baseline and follow-up clinical data for participants. The approximate remuneration will be £500 plus support costs provided by the national clinical research network. Community pharmacies will be remunerated for undertaking training and setting up the site for recruitment, consenting patients, collecting data and intervention delivery. The approximate remuneration will be £100 per patient with an estimated 30 participants per pharmacy.

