## Assignment of interventions: allocation

### Sequence generation {16a}

All participants that provide informed consent and that are eligible for the study will be randomised by variable block randomisation, with a blinded block size of 2:4. The randomisation will be stratified per pharmacy, conducted at participant level and will be normalised for age using a group of 35–55 years and 56–75 years. The sequence generation is performed by the data management platform Castor EDC [29].

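### The sample-size chain 98 → 110 → 145 per arm does not fit an individually randomised, pharmacy-stratified trial; N = 300 can stay, but the cluster step, the loss step and the power need restating

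*Protocol article*

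**What the plan says.** All of the following is in the protocol article.

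- **Sample size {14}**, model: "The sample size calculation was based on multilevel analysis with the pharmacy, patient and time as different levels".
- **Sample size {14}**, effect: "we assumed a relative difference of 20% in medication adherence between the intervention and control group". No control value or standard deviation is given.
- **Sample size {14}**, starting point: in each group, "98 participants are needed, considering a type I error rate of 5% and power of 0.80".
- **Sample size {14}**, cluster step, justified by the study having a cluster design: "assuming an intra-correlation coefficient of 0.10, a total of 110 participants are needed in both trial arms". Neither the cluster size nor the meaning of the ICC is stated.
- **Sample size {14}**, loss step: "To adjust for an expected loss to follow-up of 25%, we will need to include 145 participants in both the intervention and control group". The total is then set at 300, half in each country.
- **Sequence generation {16a}**: "The randomisation will be stratified per pharmacy, conducted at participant level". The Discussion confirms, as its second challenge, that one pharmacy treats participants of both arms.
- **Abstract, Methods**: the setting is "40–50 community pharmacies in the Netherlands and the United Kingdom".
- **Pharmacy and general practice recruitment**, on UK pharmacies: "The approximate remuneration will be £100 per patient with an estimated 30 participants per pharmacy".

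**The concern.** The cluster step rests on a design that the allocation section does not describe. When both arms are recruited and randomised inside each pharmacy, a pharmacy effect common to both arms cancels from the treatment contrast. Inflation is then needed only if outcomes cluster separately within each arm of a pharmacy, or if the treatment effect varies between pharmacies. The article claims neither. The size of the inflation also does not follow from the cluster sizes that the article gives.

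At stake is the stated power of 0.80. A reader cannot tell which source of clustering the 110 protects against, and the power of the planned 300 differs between the possible readings.

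**Working it through.** **Inputs.** 98 and 110 per arm, ICC 0.10, 25% loss, 145 per arm and 300 in total (Sample size {14}); 40–50 pharmacies (Abstract); about 30 participants per UK pharmacy (Recruitment); 1:1 allocation (Trial design {8}). A two-sided 5% test is assumed. The 98 cannot be re-derived without a standard deviation, so I take it as given and use the standardised difference that it implies.

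**Implied effect.** d = (1.960 + 0.842) × √(2/98) = 0.400.

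**Implied cluster size.** The design effect is 110/98 = 1.122. From 1 + (m − 1) × 0.10 = 1.122, m = 2.22.

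**Reproducing 110.** Take a cluster to be one arm within one pharmacy. With 50 equal pharmacies, m = 110/50 = 2.2, the design effect is 1.12, and 98 × 1.12 = 109.8, which rounds up to 110.

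If the inflated n also sets the cluster size, then n = 98 × [1 + (n/J − 1) × 0.10], so n = 88.2 / (1 − 9.8/J) for J pharmacies:

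- J = 50: 88.2/0.804 = 109.7, so 110
- J = 45: 88.2/0.782 = 112.8, so 113
- J = 40: 88.2/0.755 = 116.8, so 117

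The stated figure is therefore recovered at the top of the pharmacy range, and only with equal sites.

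**Equal sites against the UK figure.** 150 UK participants at 30 per pharmacy is 5 pharmacies, which leaves 35–45 Dutch pharmacies for the other 150. A UK site would hold about 15 per arm enrolled, or 11.25 analysed after 25% loss, not 2.2.

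**Loss step.** 110/0.75 = 146.7, so 147. The stated 145 leaves 145 × 0.75 = 108.75 analysed, 1.25 short of 110. The planned 150 per arm leaves 112.5 and tolerates 1 − 110/150 = 26.7% loss.

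**Power at 112.5 analysed per arm.** Power = Φ(d × √(n_eff/2) − 1.960), with n_eff = 112.5 / design effect. In the last two rows, n_eff is the sum of the two countries, each with its own design effect.

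| Reading | Analysed per cluster | n_eff per arm | Power |
|---|---|---|---|
| Individual randomisation, common effect | – | 112.5 | 85% |
| Pharmacy-by-arm, 50 equal sites | 2.25 | 112.5/1.125 = 100.0 | 81% |
| Pharmacy-by-arm, 40 equal sites | 2.81 | 112.5/1.181 = 95.2 | 79% |
| Pharmacy-by-arm, 5 UK + 45 Dutch sites | 11.25 and 1.25 | 56.25/2.025 + 56.25/1.025 = 82.7 | 73% |
| Pharmacy-by-arm, 5 UK + 35 Dutch sites | 11.25 and 1.61 | 56.25/2.025 + 56.25/1.061 = 80.8 | 72% |

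The first row takes no credit for removing between-pharmacy variance. If 98 was based on total variance, the need would fall to 98 × 0.9 = 88 per arm; the article does not say whether it was.

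**The case against.** The authors could answer that 110 is a deliberate allowance and not a slip. The pharmacist delivers the intervention and the pharmacy assistant handles the control contact, so clustering by pharmacy and arm is coherent. That reading returns 110 at 50 pharmacies. It also does so at 45 if the uninflated number sets the cluster size (98/45 = 2.18, design effect 1.118). The mention of a cluster design may mean only that patients are nested in pharmacies. For plain individual randomisation, 110 errs on the safe side. The loss slip is two per arm, and 150 per arm absorbs it. The calculation also cites a source and a time level that the article does not detail.

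Most of this stands, and it rules out two stronger readings. A reader might infer that 110 corresponds to no design at all; the pharmacy-by-arm reading shows otherwise. A reader might also infer that the trial is clearly underpowered, because whole-pharmacy clusters (220/50 = 4.4 to 220/40 = 5.5 analysed) would need 132–143 per arm. That is the inflation for a trial that randomises pharmacies, which the allocation section rules out.

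What the objection does not answer is that the pharmacy-by-arm definition appears nowhere in the article, that it needs equal sites and the upper end of the pharmacy count, and that the article's own UK estimate contradicts equal small sites. The five-site figure is an inference from one estimate in a remuneration paragraph, so the 72–73% is conditional. The unseen detail behind 98 does not affect the steps from 98 to 110 and from 110 to 145.

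**Conclusion.** The paragraph is wrong as written, but the sample size is not shown to be inadequate. The cluster inflation does not match the stated randomisation. Its size fits only an unstated definition of cluster that conflicts with the UK site size, and 145 should be 147.

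Under individual randomisation with a common treatment effect, the planned 300 gives about 85% power, above the stated 80%. Only if the ICC of 0.10 describes clustering by pharmacy and arm does power depend on site sizes: close to 80% with equal sites, and about seven to eight percentage points below the target with five UK sites of 30. These figures assume a two-sided 5% test, a standardised difference of 0.40, exactly 25% loss in each arm and country, and, for the lowest figures, five UK sites.

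**What to change.** Rewrite the Sample size paragraph and keep N = 300:

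1. Say that patients are nested in pharmacies but randomised individually within them, and that a common treatment effect needs no cluster inflation of the 98 per arm.
2. Correct 145 to 147, or base the loss step directly on 150 per arm (112.5 analysed).
3. Restate the power for 112.5 analysed per arm: about 85% at a standardised difference of about 0.40. State the sidedness of the test.
4. If the ICC of 0.10 is meant as pharmacy-by-arm clustering, say so, give the cluster sizes, and report power with the real unequal sites. On present figures that is about 79–81% with 40–50 equal pharmacies and about 72–73% with about five UK sites of 30.
5. Reconcile the UK estimate of 30 per pharmacy with the cluster size used.

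The cost is one paragraph and no participants. If step 4 applies, a less favourable power figure has to be shown.
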